### Trial management

The principal investigator ([name]) will oversee the conduct and progress of the trial. The principal investigator will screen the daily admission to ICU lists and liaise with the treating medical teams to optimise participant enrolment. No interim analyses are planned. The principal investigator will ensure all research personnel are appropriately orientated and trained, oversee recruitment and report to a trial safety monitoring committee who will monitor the progress and conduct of the trial. The trial safety monitoring committee will include: a physiotherapist and researcher experienced in the safe conduct of clinical trials with physiotherapy interventions; the trial coordinator and principal investigator; a critical care nurse who is also experienced in the safe conduct of clinical trials in critical care settings; and two ICU medical consultants experienced with the safe conduct of clinical trials in ICUs. One of the ICU medical consultants is employed externally to the study site. The principal investigator will provide an update report to the safety monitoring committee on a monthly basis (and additional ad hoc reports if an adverse event occurs). Additionally, any serious adverse events will be reported to the approving Metro South Human Research Ethics Committee that is overseeing the study. During in-bed cycling sessions, participants will be monitored for adverse events that will be recorded on the session data collection form. Adverse events that are being monitored for are: line or airway dislodgement, increase in ventilatory support that persists longer than 5 min post exercise (eg, increase in positive end expiratory pressure or fraction of inspired oxygen), blood oxygen desaturation less than 88% for more than 1 min, increase in vasoactive or pain relief medication greater than 5 mcg/min, increase in systolic blood pressure greater than 180 mm Hg for more than 2 min, increase in heart rate greater than 140 bpm for more than 2 min, decrease in mean arterial blood pressure less than 60 mm Hg for greater than 2 min and decrease in heart rate less than 50 bpm for more than 2 min.

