### Study intervention

All study patients will receive usual physiotherapy interventions while in intensive care. Physiotherapy interventions will include (but are not limited to): respiratory physiotherapy, physical rehabilitation exercise interventions including sitting on the edge of the bed, sit to stand transfers, sitting out of bed and walking. Usual care physiotherapy interventions will be prioritised over the in-bed cycling intervention. Safety guidelines (see box 1) will be used to determine if the intervention group patients are able to complete an additional daily 30 min progressive lower limb in-bed cycling using a bedside cycle ergometer (MOTOmed Letto 2). The lead physiotherapist ([name]) who has over 10 years of experience in rehabilitative exercise with patients with critical illness will primarily conduct the majority of in-bed cycling sessions. He has been trained by industry cycle ergometry representatives and has over 5 years of experience conducting in-bed cycling sessions with patients with critical illness. Experienced ICU physiotherapists trained in conducting in-bed cycling sessions may conduct the in-bed cycling sessions if the lead physiotherapist is unavailable. During the in-bed cycling exercise interventions, the patients’ vital signs will be monitored. If the intervention group patients are in a state of low arousal or sedated, they will cycle continuously and passively at the default passive speed of the cycle ergometer (20 revolutions per minute) for 30 min. When the participant is following commands, the clinician will verbally encourage the patient to complete in-bed cycling sessions actively for a duration of 30 min. Once the patient can cycle actively, the resistance applied by the cycle ergometer will be adjusted to facilitate patient intensity between 3 and 5 using the visual Borg scale rate of perceived exertion (category ratio 10),^14^ within the specified safety guidelines. An exercise intensity of 3–5 on the Borg rate of perceived exertion scale has been shown to be safe and feasible with patients with critical illness.^15^ This will enable the patient to cycle in-bed either passively or actively with assistance from the cycle ergometer. If a patient unexpectedly commences active cycling, the additional active in-bed cycling safety criteria will become relevant. If the patients are deemed unsuitable to continue active in-bed cycling, they will be asked to resume passive cycling. If the patient continues to actively cycle, the session will be ceased. The in-bed cycling sessions will continue until the patient completes a minimum of five in-bed cycling sessions, unless the patient is discharged from hospital prior to completing five sessions. The intervention will continue in the acute hospital ward if the patient is discharged from ICU prior to completing five in-bed cycling sessions. While the patient remains in ICU, in-bed cycling sessions will continue (up to 7 days/week), up to 28 days post-ICU admission. This frequency is congruent with usual physiotherapy services that can provide rehabilitative exercise interventions to ICU patients up to 7 days/week. Patients randomised to the usual care arm do not routinely complete in-bed cycling sessions during their hospitalisation. Any deviations from the planned protocol will be recorded to enable appropriate intervention description and, if indicated, a per-protocol analysis (in addition to the primary intention-to-treat analysis).

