### Data collection

The study data will be collected at the time points summarised in table 3.

**Table 3 T3:** CYCLIST summary of time points of assessments

	Baseline	Day 3	Day 7	Day 10	ICU discharge	1 week post ICU discharge*	3, 6 months’ post ICU-admission
Severity of illness							
APACHE III	✓						
SOFA	✓	✓	✓	✓	✓		
Muscle morphology							
Quadriceps ultrasonography	✓	✓	✓	✓		✓	
Strength measures							
MRC sum score					✓	✓	
Handgrip dynamometry					✓	✓	
Physical function measures							
ICU mobility scale					✓		
FSS-ICU					✓		
Functional milestones	✓	✓	✓	✓	✓	✓	
6-MWT						✓	
Cognition							
CAM-ICU	✓	✓	✓	✓	✓		
Quality of life							
EQ-5D-5L				✓			✓
Acceptability of intervention							
Participant acceptability				✓†			
Patient outcomes							
ICU length of stay					✓		
Hospital length of stay						✓‡	
Acute discharge destination						✓‡	
Mortality					✓	✓‡	✓

*1-week post-ICU discharge or at acute hospital discharge if sooner.

†At completion of in-bed cycle ergometry sessions.

‡Measured at acute hospital discharge.

6-MWT, 6 min walk test; APACHE, Acute Physiology and Chronic Health Evaluation; CAM-ICU, Confusion Assessment Method for the Intensive Care Unit; CYCLIST, Critical Care Cycling Study; EQ-5D-5L, EuroQol Five Dimensions questionnaire Five Levels scale.; FSS-ICU, Functional Status Score for the Intensive Care Unit; ICU, intensive care unit; MRC, Medical Research Council; SOFA, Sequential Organ Failure Assessment score.

The management of study data will be dependent on the type of data collected. Baseline data will be entered directly into REDCap-designed digital clinical trial workflow management software.^13^ Ultrasound results will be uploaded onto the secure hospital-based AGFA IMPAX 6.5.3.1005 Medical Image Viewer application. In-bed cycling session data, physical assessment measures, acceptability of in-bed cycling intervention and quality of life questionnaires will be recorded initially onto research data sheets. All information recorded on data sheets will be subsequently entered into the REDCap application.

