If blinded sonographers are unable to complete an ultrasound measurement at designated time points, then the scan will be performed within a day (±1 day) of the designated time point. A subsequent sensitivity analysis will be conducted to determine if there is a difference by measurement timing. If the primary outcome cannot be collected by a sonographer within the specified time frame, a physiotherapist experienced in musculoskeletal ultrasound will measure thigh muscle size. The measurement will be from the most anterior aspect of rectus femoris to the anterior surface of the femur. This will assist in the imputation of the missing primary outcome data. Statistical analysis of available data will be used for the primary analysis when data are completely missing. Multiple imputation will be conducted if more than 20% of outcome data are missing. Additional planned secondary analyses are listed in box 2. The principal investigators will determine if study protocol modifications are required and any modifications to the existing protocol will be declared.Box 2Planned secondary analysesMuscle wasting at baseline, day 3, day 7 and 1 week post-ICU dischargeMuscle wasting adjusted for number of failing vital organs*Muscle wasting adjusted for severity of illness on admission to ICU†Muscle wasting adjusted for the number of days prior to a patient commencing active activityMuscle wasting adjusted for the patients’ cumulative fluid balance on the day of the ultrasound scanRelationship between muscle wasting and participants’ nutritional intake while in ICURelationship between sedative and paralytic medications and muscle wastingCost comparison of hospitalisation for both the intervention and usual care groups‡Hospital readmissions after acute hospital discharge over a 2-year time period§Mortality¶Utilising:*Sequential Organ Failure Assessment (SOFA).†APACHE III (Acute Physiology and Chronic Health Evaluation) data.‡Health service utilisation data.§Queensland Hospital Admitted Patient Data Collection (QHAPDC).¶Queensland Health Statistical Services Branch.ICU, intensive care unit.

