CYCLIST is a phase IIb RCT that is powered to investigate if the early application of an additional in-bed cycling intervention is able to reduce the rate of skeletal muscle atrophy of patients’ quadriceps muscle during and immediately following a period of critical illness, in comparison to usual care. Secondary outcomes evaluated in this study will assist sample size calculations for future studies to assess for efficacy of functional outcomes. The study will also aid planning of future rehabilitation-based clinical trials with regard to rate of participant recruitment. The investigators are planning to meet at the completion of the study to facilitate reflection on aspects of the study that could be improved and to consider whether a definitive phase III RCT is warranted. This will include consideration of the evidence of effect on primary and secondary outcomes, participant recruitment and adherence to the in-bed cycling protocol and rate, as well as acceptability of the intervention.

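### The listed adverse events are captured through cycling sessions only, so their counts form a single-arm, per-session rate that cannot show whether cycling adds harm

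*Protocol article*

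**What the plan says.** Under Trial management, the protocol article gives the capture rule for adverse events: "During in-bed cycling sessions, participants will be monitored for adverse events that will be recorded on the session data collection form". Eight kinds of event follow: line or airway dislodgement, a lasting rise in ventilatory support, desaturation, a rise in vasoactive or pain-relief medication, high systolic pressure, fast heart rate, low mean arterial pressure and slow heart rate. One of them reaches beyond the session itself: "increase in ventilatory support that persists longer than 5 min post exercise".

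Under Study intervention: "Patients randomised to the usual care arm do not routinely complete in-bed cycling sessions during their hospitalisation". The Discussion adds that the content and amount of usual-care physiotherapy are not recorded prospectively.

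Other parts of the plan bear on harm and carry no limit by arm or session:

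- Trial management: "any serious adverse events will be reported to the approving Metro South Human Research Ethics Committee that is overseeing the study". The safety committee receives monthly updates and "additional ad hoc reports if an adverse event occurs".
- Data collection, Table 3 ("CYCLIST summary of time points of assessments"): SOFA at baseline, days 3, 7 and 10 and ICU discharge; CAM-ICU at the same points; mortality at ICU discharge, hospital discharge, and 3 and 6 months.
- Analysis, Box 2: mortality, and "Hospital readmissions after acute hospital discharge over a 2-year time period".

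**The concern.** Low blood pressure, tachycardia, desaturation and a need for more ventilatory or vasoactive support are common features of critical illness. They can arise in a ventilated patient during any half hour, with or without cycling. An event seen during a session can be attributed to cycling only if one knows how often the same event occurs in a comparable window without it. The trial has randomised controls in the same unit who could supply that reference, but the capture rule does not reach them.

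Two misreadings then become possible. Session events set beside an empty usual-care column would look like harm from cycling, although the empty column reflects only the lack of a form. Conversely, a low session count could be taken as proof that cycling adds no risk, which a count without a comparator cannot show. Events that come to light after a session, such as a displaced line noticed later or a new thrombosis, have no stated place on the form unless they are the ventilatory-support item. Box 1 treats acute DVT or PE as a bar to exercise, yet new thrombosis is not among the listed events.

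**Working it through.** The plan gives no figure for adverse events, so there is none to reproduce. The point rests on reading the sections together; the arithmetic only shows scale.

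**Who can register a listed event**

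| | Cycling arm | Usual-care arm |
|---|---|---|
| Cycling session (Study intervention) | Daily when the safety criteria allow, minimum of five unless discharged from hospital sooner | Not routine |
| Session form (Trial management) | Yes | None, as there is no session |
| Parallel record of physiotherapy (Discussion) | Not prospectively recorded | Not prospectively recorded |
| Listed event after the session | Ventilatory-support item only | No stated route |
| Serious adverse event to the ethics committee | Yes | Yes, no arm limit stated |
| SOFA, CAM-ICU, mortality, readmissions | Yes | Yes |

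The first four rows show that the listed events are bound to one arm. The last two show that other harm data are not.

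**Scale of the missing background rate**

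Inputs: 34 patients per arm (Sample size); five sessions each (the minimum in Study intervention); background probability q of a listed event in one session window, assumed to be 1%, 2% or 5% because the document gives no figure.

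- Sessions: 34 × 5 = 170.
- Expected events with no effect of cycling: 170 × 0.01 = 1.7; 170 × 0.02 = 3.4; 170 × 0.05 = 8.5.
- Recordable on the session form in usual care: none.

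The figure of 170 is nominal. Sessions may continue in ICU up to day 28, and some patients will not reach five. Box 1 also withholds sessions from unstable patients, so q in a session window may be lower than in an unselected ICU half hour.

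**What a clean record would show**

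The one-sided 95% upper bound after zero events in n independent trials is 1 − 0.05^(1/n).

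- Sessions independent, n = 170: 1 − 0.05^(1/170) = 1.75% per session.
- Extreme opposite case, sessions within a patient fully dependent, n = 34: 1 − 0.05^(1/34) = 8.4%.

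Either bound limits the total event rate during cycling. Neither says how much of it exceeds background.

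**What capture in both arms could achieve**

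The normal-approximation power for two proportions, two-sided 5%, n = 34 per arm, is Φ{[|p1 − p2| − 1.96√(2p̄(1 − p̄)/n)] / √[(p1(1 − p1) + p2(1 − p2))/n]}. With assumed rates:

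| Usual care | Cycling | Power |
|---|---|---|
| 5% | 15% | 0.28 |
| 10% | 30% | 0.54 |
| 20% | 40% | 0.43 |

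Even large differences would often be missed, so a by-arm table would be descriptive.

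**The case against.** A fair defence has several parts.

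- A reader might infer that adverse events are recorded solely during sessions and that nothing later can be detected. The text does not support this. Serious adverse events go to the ethics committee without limit by arm or session, the ad hoc reports to the safety committee carry no arm limit, and one listed event is defined by what happens after exercise.
- A reader might also infer that the trial offers no randomised comparison of harm. It does: mortality, organ failure, delirium and readmission can all be compared by arm.
- A third inference is that the decision on a further trial, "to consider whether a definitive phase III RCT is warranted", would rest on the session count. The Discussion names effects on outcomes, recruitment, adherence and acceptability; adverse events are not named.
- No by-arm table of session events is planned, and a per-session rate is a conventional measure of tolerability.
- The article condenses a fuller protocol, which may hold a wider adverse-event procedure.

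The first three parts stand and limit the point. The fourth stands in part: no misleading table is planned, but nothing in the article says the counts are not for comparison. The fifth does not remove the point, because the article states a capture rule rather than leaving one out, and that rule operates in one arm. Nor do the both-arm data fill the gap: SOFA on fixed days and mortality do not record a dislodged line or a short fall in pressure, and a duty to report serious events is not a described search for them in both arms.

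**Conclusion.** The point holds in a limited form. As written, the listed events yield a single-arm, per-session rate with no background rate, and apart from the ventilatory-support item no post-session window is stated. Such a rate describes tolerability of the sessions but cannot show whether cycling adds harm.

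The consequence is modest. Safety is neither a stated objective nor a listed outcome, the primary analysis of rectus femoris area is unaffected, and the more serious harm data are open to both arms. The expected counts of 1.7 to 8.5 depend on assumed background risks and a nominal 170 sessions; they illustrate the problem and do not estimate it. The conclusion also assumes that no both-arm procedure exists in a full protocol that is not shown. This is a worthwhile low-cost improvement to the safety reporting, not a threat to the trial's main result.

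**What to change.** 1. Keep the session form and report its events as a rate per session. State that these events are single-arm and will not be compared between arms.
2. In both arms, from randomisation to ICU discharge, abstract a short list from routine ICU charts and incident reports: airway or line dislodgement, unplanned extubation, new DVT or PE, serious adverse events and death.
3. Report this list descriptively by arm, per ICU day.

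The cost is added abstraction time for the existing team and one more table, with no extra patients or procedures. Two limits should be stated with it: the transient physiological events (pressure, heart rate, saturation, ventilatory or vasoactive support) remain single-arm, and with 34 patients per arm the comparison has little power and is descriptive only. If the abstraction is judged too much, the statement in step 1 costs nothing and alone guards against a misleading by-arm reading.

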Box 1Safety guidelinesActive or passive exercise should not be delivered if:Clinician’s opinion that patient’s condition is unstableResting HR<40 or >120 bpm or new arrhythmiaEvidence of coronary ischaemia, for example, chest pain or ECG changesMAP<60 or SBP>200 mm HgSpO_2_<90%RASS≥2Wounds of leg, pelvis or lumbar spine precluding cycle ergometryEvidence of active bleeding or coagulation disorder: INR>1.8, PLT<50 000/µL*Femoral vascular access†, for example, dialysis catheter, IABP, ECMO or lower limb arterial line‡Acute DVT or PEActive exercise should not be delivered if:>20 µg/min of norepinephrine or comparable inotropic or vasopressor supportFiO_2_>0.55 or PEEP>10 cmH2ORR>30 with adequate ventilatory supportTemperature >39°CStopping criteria: active or passive exercise should cease if:HR<50 or >140 bpm, or new arrhythmia develops (including ventricular ectopic or new-onset AF)Evidence of coronary ischaemia, for example, chest pain or ECG changesMAP<60 mm HgSBP>200 mm HgClinical signs of cardiorespiratory distressSpO_2_<90% for more than 1 minPatient’s request to stop therapy*Values outside this range would be tolerated if patient is therapeutically anticoagulated.†Other than femoral central line.‡If a femoral vascular access is inserted unilaterally the contralateral leg may be cycled unilaterally.AF, atrial fibrillation; bpm, beats per minute; DVT, deep vein thrombosis; ECMO, extracorporeal membrane oxygenation; FiO_2_, fraction of inspired oxygen; HR, heart rate; IABP, intra-aortic balloon pump; INR, international normalised ratio; MAP, mean arterial pressure; PE, pulmonary embolism; PEEP, positive end expiratory pressure; PLT, platelets; RASS, Richmond Agitation Sedation Score; RR, respiratory rate; SBP, systolic blood pressure; SpO_2_, saturation of peripheral oxygen.

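### The list of adverse events monitored during cycling sessions is worded as complete but names neither coronary ischaemia nor new arrhythmia, although Box 1 says exercise should cease for either.

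*Protocol article*

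**What the plan says.** All references are to the protocol article.

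- **Trial management, recording.** During cycling sessions "participants will be monitored for adverse events that will be recorded on the session data collection form".
- **Trial management, list.** The next sentence opens "Adverse events that are being monitored for are: line or airway dislodgement" and continues with seven more items. These cover ventilatory support, oxygen saturation, medication ("increase in vasoactive or pain relief medication greater than 5 mcg/min"), systolic pressure, high heart rate, mean arterial pressure and low heart rate. The sentence ends there. Nothing marks the items as examples, and there is no residual category.
- **Trial management, reporting.** The safety monitoring committee receives a monthly update, with "additional ad hoc reports if an adverse event occurs". Serious adverse events of any type go to the ethics committee.
- **Box 1 (Participants section).** The stopping criteria begin "active or passive exercise should cease if". One criterion is coronary ischaemia, with chest pain and ECG changes as examples. Another pairs heart rate limits with a rhythm trigger: "new arrhythmia develops (including ventricular ectopic or new-onset AF". Both conditions also appear in Box 1 as reasons not to start.
- **Study intervention.** "Any deviations from the planned protocol will be recorded to enable appropriate intervention description".
- **Data collection and Discussion.** Session data go onto research data sheets and then into REDCap. The Discussion expects compliance and completion rates to inform feasibility.

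**The concern.** Box 1 treats ischaemia and new arrhythmia as hazards of the exercise itself, since each bars a session from starting and each ends one in progress. The same article then sets out which session events are monitored and names neither. The wording is that of a finished list with thresholds and durations, so this is not simply a detail left to a fuller document.

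What is at stake is the completeness of the safety record. A non-serious cardiac reaction could end a session, fall outside the monitored events, and so perhaps prompt no ad hoc report to the committee. The Discussion says the investigators will use the trial to consider whether a phase III study is warranted. A tabulation of session events that need not contain two of the protocol's own cardiac reasons for stopping is a weaker basis for that decision.

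**Working it through.** The document gives no figure to reproduce. The check sets the two lists side by side and then tests one case.

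**Step 1. Box 1 stopping criteria against the monitored events**

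| Box 1: stop if | Nearest monitored event |
|---|---|
| HR <50 or >140 bpm | HR <50 or HR >140 bpm, each for over 2 min |
| New arrhythmia (printed as part of the HR criterion) | None |
| Coronary ischaemia | None |
| MAP <60 mm Hg | MAP <60 mm Hg for over 2 min |
| SBP >200 mm Hg | SBP >180 mm Hg for over 2 min |
| Cardiorespiratory distress | Not named; reached indirectly through saturation, support, heart rate or pressure items |
| SpO2 <90% for over 1 min | SpO2 <88% for over 1 min |
| Patient asks to stop | None (not a physiological sign) |

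The monitored list has eight items: dislodged line or airway, raised ventilatory support, SpO2, raised medication, SBP, high HR, MAP and low HR. The dislodgement, support and medication items have no counterpart among the stopping criteria.

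**Step 2. Count.** Box 1 prints seven stopping criteria, because arrhythmia shares a line with heart rate. Without patient request, 7 − 1 = 6 are physiological. Two triggers clearly have no counterpart: ischaemia, which is a whole criterion, and arrhythmia, which is part of one. Whether cardiorespiratory distress is a third is a matter of judgement. It is not named, but its usual signs would often trip a listed item.

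**Step 3. Test case.** Suppose new-onset AF develops in a session at 120 bpm. The rate is an assumption chosen for illustration. Blood pressure, saturation, ventilatory support and medication are unchanged, and nothing is dislodged.

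- Box 1: a new arrhythmia, so exercise should cease.
- High HR item: 120 is not above 140, so not met.
- Low HR item: 120 is not below 50, so not met.
- The other six items: not met by construction.
- Result: a stop, with 0 of 8 monitored events.

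The same result holds for any new arrhythmia at a rate from 50 to 140 bpm, or outside that range for no more than 2 min, if the other parameters hold. It also holds for chest pain or an ECG change without haemodynamic change that needs no listed increase in medication.

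**Step 4. Other routes by which the event could be captured**

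- *Deviation record (Study intervention).* Ceasing under Box 1 follows the protocol, and the article does not say that such a session is a deviation.
- *Session data and completion rates (Data collection, Discussion).* A 30 min session cut short would probably show as incomplete. Neither place says that the reason is kept.
- *Ad hoc committee reports.* This sentence comes before the list and is not expressly limited to it, so a report might still be made.
- *Serious adverse events.* These are reported whatever their type, so a serious ischaemic or arrhythmic event is covered.

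What is left is the non-serious cardiac reaction with no listed parameter crossed. Its occurrence may leave a trace, but no stated route records what it was.

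**The case against.** The strongest reply is that a stopping rule and an adverse event definition do different jobs and need not match. Box 1 is precautionary; most monitored events require a larger or longer change. Saturation stops exercise below 90% but is an event only below 88%. The heart rate and MAP limits stop exercise at once but become events only after 2 min. Systolic pressure runs the other way: the event limit is 180 and the stop limit 200. Box 1 also counts a ventricular ectopic as a trigger, and few would want every ectopic logged as an adverse event. This stands. A reader might infer that the protocol contradicts itself, and the documents do not support that, because nowhere do they say that every stop is an event.

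A reader might also infer that such reactions would go unrecorded and unreported. That is not supported either. The session form is not shown and may hold a stop-reason or free-text field, the ad hoc reporting sentence is not tied to the list, the committee reports monthly, and serious events have their own route.

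Nor should the stops be called mandatory. Box 1 is headed as guidelines and says that exercise should cease.

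None of this closes the gap. The different thresholds explain why a brief drop in saturation might stop a session without being an event. They do not explain why ischaemia has no place on the list at any severity. And none of the alternative routes states that the cardiac event, or the reason for stopping, is written down.

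**Conclusion.** The point holds as a minor gap in safety recording. The monitored list is worded as complete and leaves out two cardiac triggers for which Box 1 says exercise should cease, so a non-serious reaction of either kind can end a session without being a monitored adverse event.

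This assumes that the list is applied as written and that the session form has no field that already captures the reason for stopping. The first is the plain reading; the second cannot be checked from the article. The document gives no frequency for such stops, so the number of events affected is unknown.

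Participants are not less protected during the session, since exercise should stop either way. The primary outcome, power and type I error are unaffected.

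**What to change.** 1. Add coronary ischaemia and clinically significant new arrhythmia to the monitored session events. The investigators and the safety monitoring committee should define which arrhythmias count, so that an isolated ectopic is not automatically an event.
2. If the session form does not already do so, record the Box 1 reason for every ceased session, including cardiorespiratory distress, and include these in the monthly report to the committee.

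The cost is two items of protocol wording, one or two fields on an existing form and a line in the monthly report. The reported event count may rise slightly. Nothing in the design, sample size or analysis changes.
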